#### Primary outcomes

There are two types of primary outcomes that will be evaluated:The *primary feasibility outcomes* will be recruitment and retention rate for eligible patients and the estimated resources required per patient to complete the main trial (program delivery costs). We aim for at least 30% recruitment of those eligible, 90% retention of those recruited, and no more than US $1500 per patient spent on running the pilot trial. This figure is based on the limits of peer-reviewed RCT funding for a full trial.The *primary clinical outcome* will be the number of drug therapy problems remediated including the number of high-risk medications improved (for example, dose adjustment, discontinued, seriously interacting drugs removed) at 3-month posthospital discharge end-study visit, as judged by adjudicators using APEQ.

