**Methods:**

The design is a pragmatic pilot randomized trial with 1:1 patient-level concealed randomization with blinded outcome assessment and data analysis. Participants will be adults 65 years and older admitted to internal medicine services for more than 2 days, who have had at least one other hospitalization in the prior year, taking five or more chronic medications including at least one high-risk medication. The CPT intervention identifies medication targets; completes consult, including priorities for improving prescribing negotiated with the patient; starts the care plan; ensures a detailed discharge medication reconciliation and circle-of-care communication; and sees the patient at least twice after hospital discharge via virtual visits to consolidate the care plan in the community. Control group receives usual care. Primary outcomes are feasibility — recruitment, retention, costs, and clinical — number of drug therapy problems improved, with secondary outcomes examining coordination of transitions in care, quality of life, and healthcare utilization and costs. Follow-up is to 3-month posthospital discharge.

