	**Outcome**
Feasibility	1. Participant recruitment rates
	2. Participant retention rate
	3. Trial resource utilization, costs
	4. Recommendation acceptance rates by primary team
	5. Recommendation acceptance rates by patient
	6. Recommendation adherence rates by patient
	7. CPT consultation volume capacity
	8. Potential to intervene entirely virtually (online)
Clinical	**1.** Medication management outcomes a) # inappropriate medications, # drug therapy problems improved, # high-risk medication problems improved, all measured by APEQ b) # medications per patient end study versus baseline
	**2.** Adverse drug events including adverse drug withdrawal event
	**3.** Medication errors, including preventability
	**4.** Patient problems with medications questionnaire (includes general adherence)
	**5.** Patient knowledge of medications
	**6.** Coordination and continuity of care
	**7.** Patient quality of life (EQ-5D-5L and medication-related QOL)
	**8.** Satisfaction with care (patients and providers)
	**9.** Health resource utilization, including clinical events of death, ED visits, hospitalizations, physician visits, other providers including diagnostics utilization, medication costs

**Table 2 Tab2:** IMPROVE-IT HRM study outcomes and measures

	Outcomes	Criteria for success	Outcome measure	Method of analysis	When assessed

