**A. Feasibility outcomes**					
A1. Primary feasibility outcomes	A1.1 Participant recruitment rates	≥ 30% of those eligible will be considered success	Percentage recruited and rate of recruitment (of those screened, of those eligible, and of those approached)	Counts (%) over time	Baseline
	A1.2 Participant retention rate	≥ 90% is considered success	Percentage of those recruited who complete at least end-study outcome	Counts (%) end study	End of study
	A1.3 Intervention adherence	≥ 90% is considered success	Percentage of those recruited who completed each phase of the study (baseline, virtual visits, end of study outcomes)	Counts (%) over time	End of study
	A1.4 Study resource utilization	< US $1500 per patient recruited and completing the study	Study costs per patient recruited to end follow-up	Cost of personnel, supplies, travel, etc. to run the study	End of study
A2. Secondary feasibility outcomes	A2.1 Clinical Pharmacology & Toxicology (CPT) Recommendation Acceptance — Primary Team	> 50% medication recommendations	% CPT recommendations per patient accepted (continued or implemented)	Counts (%) after consult	Hospital discharge
	A2.2 CPT recommendation acceptance — patients	> 50% medication recommendations	% CPT recommendations per patient that were initially followed by patient	Counts (%) after consult	Hospital discharge
	A2.3 CPT recommendation adherence — Patients	≥ 90% is considered success	% CPT recommendations per patient still being followed at end of study	Counts (%)	End of study
	A2.4 CPT consultation volume capacity	Number of eligible patients available to approach is > 3 per day	Volume of eligible patients available to approach per week	Counts	Baseline
	A2.5 Potential to intervene entirely virtually	> 90% patients can be managed through follow-up entirely by virtual care platform	Number (%) patients entering follow-up who do not require an unscheduled in-person visit Number of follow-up visits conducted using secure videoconference platform	Counts (%)	End of study
**B. Clinical outcomes**		**Hypothesis**			
B1. Primary clinical outcomes	B1.1 Drug therapy problems improved	Intervention group will have more improved drug therapy problems compared to control group (e.g., dose adjusted, discontinued, interacting drugs removed)	Percentage of baseline drug therapy problems identified by APEQ that have been improved by end of study	Mean difference in APEQ score changes	End of study

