### Sample size

Since this is a pilot RCT, we will aim for 30 patients per group or 60 in total as this number is likely to provide adequate evidence regarding feasibility for ramp-up to a definitive trial.

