### Data collection methods

Trained research staff will conduct interviews with the patients or caregivers, entering data electronically on study laptops directly into REDCap case report forms. The participants’ medical records will be reviewed to abstract data on baseline characteristics, medical history, and medication information. Strategies to promote participant retention and complete follow-up include reminding participants in advance of their end-of-study visit and communicating by email if email address is provided at baseline. Participants who drop out of the study will have their data to that point retained in the study, as approved by REB, to avoid bias. The reasons for study non-completion will be recorded. The SPIRIT figure outlining the schedule of enrolment, intervention, and assessment (as per evidence-based recommendations for the minimum content of a clinical trial protocol) can be found in Table 3 [89].

**Table 3 Tab3:** IMPROVE-IT HRM schedule of enrolment, intervention, and assessment

**Assessment**	**Enrolment**	**Study in-progress**				**Study end**
	**Baseline**	**Inpatient stay**	**Hospital discharge**	**1 week**	**1 month**	**3 months**
Eligibility screen	A					
IMPROVE-IT assessment of capacity to consent	B					
Informed consent	1/C					
EQ-5D-5L v10- Canada	I/C					I/C
Medication quality of life (MedQOL)	1/C					I/C
Clinical Frailty Scale	I/C					I/C
Complete medication list (prescription, OTC, other)	I/C		I/C			I/C
Medication knowledge assessment	I/C					I/C
Circle-of-care information	I		I	I	I	
Randomization and allocation	I/C					
Clinical Pharmacology Toxicology Consult		I		I	I	
Appropriateness of prescribing (APEQ) — #drug therapy problems improved, #high-risk medication problems improved, #PIMs improved	I/C					I/C
Adverse drug event assessment						I/C
Patient problems with medications						I/C
Patient/caregiver satisfaction questionnaire						I/C
Provider satisfaction questionnaire						I/C
Health Resource Utilization Questionnaire						I/C

Abbreviations: *A*-all potentially eligible patients, *B-*all eligible and interested patients, *I*-intervention, *C*-control, *I/C*-both groups

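### The primary clinical outcome is a number in the text, a percentage in Table 2 and an undefined score change in its analysis column, so there is no single primary clinical result

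*Protocol article*

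**What the plan says.** The protocol article describes the primary clinical outcome in several places.

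- **Abstract, Methods:** a number, "number of drug therapy problems improved, with secondary outcomes examining coordination of transitions in care".
- **Primary outcomes section:** a number at the 3-month end-study visit, judged by adjudicators using APEQ. The outcome "will be the number of drug therapy problems remediated including the number of high-risk medications improved".
- **Table 2, row B1.1, hypothesis:** worded as a number, "Intervention group will have more improved drug therapy problems compared to control group".
- **Table 2, row B1.1, outcome measure:** a percentage, "Percentage of baseline drug therapy problems identified by APEQ that have been improved by end of study".
- **Table 2, row B1.1, method of analysis:** a score difference, "Mean difference in APEQ score changes".
- **Table 1:** separate counts, none marked as primary: "inappropriate medications, # drug therapy problems improved, # high-risk medication problems improved, all measured by APEQ".
- **Table 3:** the same APEQ assessment, at baseline and 3 months in both arms, again with separate counts: "drug therapy problems improved, #high-risk medication problems improved, #PIMs improved".

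The Statistical analyses section gives no rule for choosing among these.

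**The concern.** A number, a percentage and a score change are different summary measures, and one table row contains all three. They respond to different features of the data.

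- The number improved scales with how many problems a patient starts with, so a chance difference in baseline burden between arms adds noise to it.
- The percentage divides that burden out. It gives a patient with 1 of 1 improved the same weight as one with 8 of 8, and it does not exist for a patient with no baseline problem.
- A baseline-to-end score change may also reflect problems that arise after baseline. This is an assumption, because the score is not defined.

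It is also unclear whether high-risk-medication problems belong to the primary outcome, as the Primary outcomes text says, or form a separate count, as Tables 1 and 3 list them.

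The abstract's Discussion makes the follow-up trial conditional partly on encouraging clinical results. If three definitions remain open, the clinical result can be picked after the data are seen. Any effect size or standard deviation carried into the definitive trial would depend on that pick.

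**Working it through.** **1. The plan's own figure.** The Sample size section says "we will aim for 30 patients per group or 60 in total", on feasibility grounds. It gives no effect size, standard deviation, alpha or power, so there is nothing to reproduce beyond 30 + 30 = 60. The sample size does not rest on this outcome.

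**2. The definitions compared.**

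| Place | Quantity | Restricted to baseline problems? |
|---|---|---|
| Abstract; Primary outcomes | Number improved or remediated | Not stated |
| Table 2 B1.1, outcome measure | Percentage improved | Yes |
| Table 2 B1.1, analysis | Difference in score change | Not stated; score undefined |

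All three are current text. A separate analysis plan could add detail, but the table row would still contradict itself and the text.

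**3. Can number and percentage differ with no baseline imbalance?** Constructed example: four patients per arm, baseline problems 8, 2, 1, 6 in both arms. Intervention improves 3, 2, 1, 2 and control improves 4, 0, 0, 3.

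- Mean number: 8/4 = 2.0 v 7/4 = 1.75.
- Mean percentage: (3/8 + 2/2 + 1/1 + 2/6)/4 = 0.677 v (4/8 + 0 + 0 + 3/6)/4 = 0.25.
- Pooled proportion: 8/17 = 0.47 v 7/17 = 0.41.

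The same data look near null on the number and large on the mean percentage.

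**4. How often would the conclusion change?** Simulation of 20,000 trials, 30 per arm, two-sided 5% t-tests as a yardstick. Baseline problems are 1 + Poisson(m − 1), so every patient has at least one. The probability of improvement is 0.166 in control, borrowed from the 16.6% addressed by discharge in the Background chart review, and 0.35 in intervention. New problems per patient are Poisson with mean 0, 0.5 or 1. Score change is read as net change in the number of problems. The 0.35, the m = 5 and the new-problem rates are assumptions.

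| Mean baseline m | Number and percentage disagree | At least one of three disagrees (new problems 0 / 0.5 / 1) |
|---|---|---|
| 2.8 | about 18% | 18% / 42% / 51% |
| 5 | about 9% | 9% / 22% / 33% |

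With no new problems, the net change and the number are the same quantity. Power for number and percentage was similar (69% v 67% at m = 2.8; 89% v 91% at m = 5), so this check does not favour either.

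**5. Patients with no baseline problem.** The chart review's 2.8 potentially inappropriate medications per person is used as a proxy for drug therapy problems, with Poisson counts. Then exp(−2.8) = 0.061, and 0.061 × 60 ≈ 3.6 patients have an undefined percentage. At a mean of 5, exp(−5) = 0.0067, and × 60 ≈ 0.4 patients.

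**6. Chance baseline difference.** Under the same proxy, the 95% range for the difference in mean baseline count is ±1.96 × √2.8 × √(2/30) = ±0.85.

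**The case against.** The strongest reply is that this is a wording slip in a feasibility pilot. Number and percentage share a numerator and will often agree after randomisation. The sample size does not depend on the outcome, and the definitive trial is to bring clinical outcomes forward as primary. Statisticians and adjudicators stay blinded until analysis is complete, which limits a choice made by result. All of this stands and it lowers the severity. It does not say which quantity is primary, and blinding limits selective choice without removing it.

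Four stronger readings are tempting and are not supported.

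- *The trial has no primary result at all.* The primary feasibility outcomes (recruitment, retention, cost) have numeric thresholds and answer the research question. Only the clinical result is affected.
- *The count is confounded by baseline imbalance.* Under concealed 1:1 randomisation, chance imbalance adds variance and not systematic bias.
- *The score change counts new problems and the other two ignore them.* The score is undefined, so its content is unknown. The count in the Primary outcomes section is not expressly limited to baseline problems either; only the percentage is.
- *The measures will point in opposite directions.* The example in step 3 shows no reversal. One can be built: intervention 2/2, 2/2, 1/2 and control 3/6, 3/6, 2/5 give mean numbers of 1.67 v 2.67 but mean percentages of 83% v 47%. That example has baseline means of 2.0 v 5.67, a gap of 3.67, more than four times the ±0.85 in step 6. Nothing in the protocol makes a reversal likely.

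The proxy in steps 5 and 6 is also weak. It counts inappropriate medications in a chart review, not drug therapy problems in patients who meet this trial's criteria of five or more chronic medications with at least one high-risk.

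**Conclusion.** The inconsistency is real and is in the current text. The primary clinical outcome is a number, a percentage and a score change, and no rule says which governs. It should be fixed, but it does not undermine the pilot: feasibility outcomes and sample size are untouched.

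The contradiction itself rests on no assumption. Its practical size does. Number and percentage led to different significance verdicts in about 9% to 18% of simulated trials. Adding a net-change reading of the score raised disagreement to between 9% and 51%, depending on assumed baseline burden and new-problem rates. These figures illustrate that the choice matters; they do not predict this trial's data.

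**What to change.** Before unblinding:

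1. Name one primary clinical variable, with its denominator.
2. State how problems arising after baseline are handled, and what happens to patients with no baseline problem.
3. State whether high-risk-medication problems are part of it or a separate secondary outcome.
4. Replace the analysis entry in Table 2, row B1.1, with one that matches the variable. If an APEQ score is kept anywhere, define it.
5. Align the abstract, the Primary outcomes section and Tables 1, 2 and 3.

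One workable choice is baseline problems improved out of the patient's baseline total, analysed with a quasi-binomial model by arm, with the other measures named as secondary outcomes. This picks one weighting and does not reconcile the measures: patients count in proportion to their number of problems, and in the example it compares 0.47 with 0.41, not 68% with 25%. Patients with no baseline problem contribute nothing, which should be stated alongside the intention-to-treat commitment. Another single, fully specified definition would serve equally well.

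The cost is wording plus a standard analysis. APEQ is already scheduled at baseline and 3 months in both arms, so no new data are needed.

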#### Secondary outcomes

The *secondary feasibility outcomes* of CPT consultation include recommendation acceptance and adherence by primary team and by patients, consult volume capacity, and potential to apply the intervention entirely through virtual visits including eConsults. Thresholds for success are described in Table 2.*The secondary clinical/patient-important outcomes* will include the following:Adverse drug events (ADEs) defined as “Harm caused by exposure to a drug” adjudicated using Leape and Bates scale (6 - definitely due to medication, 5 - probably due to medication, 4 - possibly due to medication, 3 - possibly due to disease, 2 - probably due to disease, 1 - definitely due to disease, 5 and 6 considered ADE) [74]. ADE preventability will be evaluated using the recommended “best practice”-based definition [70].Medication errors defined as an error (of commission or omission) at any step along the pathway that begins with prescribing and ends with the patient taking the medication [74]. We will use the standard NCC-MERP classification system [71, 75].Number of medications per patient end study compared to baseline.Patient problems with medications: The COMPETE Medication Problems Questionnaire measures problems with medication access, handling, beliefs, and adherence [76].Medication knowledge assessment: This will be assessed using the Medication Knowledge Assessment form, which tests knowledge of medication name, indication, dosage instructions, and precautions [77].Coordination and continuity of care: Adapted from Health Quality Ontario’s draft guidance and a Rand instrument, the Coordination and Continuity of Care Questionnaire is designed to measure the quality of the transitional and follow-up care. We will focus on medication reconciliations and education and circle-of-care communications [78, 79].Patient quality of life: We will use the general EQ-5D-5L, a five-level measure of health status and utilities well validated in Canada and based on self-reported mobility, self-care, usual activities, pain discomfort, and anxiety/depression [80–82]. We will also use a “condition-specific” QOL measure, the medication-related quality-of-life measure which is designed for people living with polypharmacy [83].Satisfaction with care: Satisfaction reported by patients and by key health professionals is one of the recommended outcomes to report in medical research, as it may influence adherence [84, 85]. This outcome will be assessed by the Patient/Caregiver Study Satisfaction Survey and by the Provider Study Satisfaction Survey [86].Health resource utilization: This is a key outcome to determine cost-effectiveness and cost-utility which then determines whether healthcare systems might pay for this type of care [87, 88]. Using questionnaire and chart review, we will capture emergency department visits, hospitalizations, unplanned physician visits, and medication costs, including out-of-pocket medication costs in follow-up [79, 88].

Outcome data will be collected by research staff through a mix of patient interview and chart review. All adjudication will be carried out blinded to group allocation of the patient. Completeness of data for variables including sex, gender, age, social support, socioeconomic status, cognition, number of medications, and comorbidities will be examined as these are potential predictors of outcomes. Sensitivity analyses will assist with determination of potential for cost-effectiveness of the intervention overall and in selected subgroups.

Geographic wards in the hospital allow for evaluation of the intra-cluster correlation (ICC), which based on past experience, we expect to be low [76]. Additionally, barriers and facilitators to the success of the primary outcomes and potential for scalability to a larger trial will be assessed in weekly team meetings.

### Follow-up

Patients will be followed until 3-month posthospital discharge or until death or admission to long-term care home, whichever occurs first. Follow-up visits will be conducted by videoconference via Epic EMR or Ontario Telehealth Network, or by phone call, depending on the patient’s digital technology capability.

### Sample size

Since this is a pilot RCT, we will aim for 30 patients per group or 60 in total as this number is likely to provide adequate evidence regarding feasibility for ramp-up to a definitive trial.

### Blinding

As a pragmatic RCT layered on routine clinical care, it will not be possible to completely blind patients or their providers; however, outcome data collectors, adjudicators, and statisticians will be blinded to group allocation until analysis is completed at the end of the study.

### Data collection methods

Trained research staff will conduct interviews with the patients or caregivers, entering data electronically on study laptops directly into REDCap case report forms. The participants’ medical records will be reviewed to abstract data on baseline characteristics, medical history, and medication information. Strategies to promote participant retention and complete follow-up include reminding participants in advance of their end-of-study visit and communicating by email if email address is provided at baseline. Participants who drop out of the study will have their data to that point retained in the study, as approved by REB, to avoid bias. The reasons for study non-completion will be recorded. The SPIRIT figure outlining the schedule of enrolment, intervention, and assessment (as per evidence-based recommendations for the minimum content of a clinical trial protocol) can be found in Table 3 [89].

**Table 3 Tab3:** IMPROVE-IT HRM schedule of enrolment, intervention, and assessment

**Assessment**	**Enrolment**	**Study in-progress**				**Study end**
	**Baseline**	**Inpatient stay**	**Hospital discharge**	**1 week**	**1 month**	**3 months**
Eligibility screen	A					
IMPROVE-IT assessment of capacity to consent	B					
Informed consent	1/C					
EQ-5D-5L v10- Canada	I/C					I/C
Medication quality of life (MedQOL)	1/C					I/C
Clinical Frailty Scale	I/C					I/C
Complete medication list (prescription, OTC, other)	I/C		I/C			I/C
Medication knowledge assessment	I/C					I/C
Circle-of-care information	I		I	I	I	
Randomization and allocation	I/C					
Clinical Pharmacology Toxicology Consult		I		I	I	
Appropriateness of prescribing (APEQ) — #drug therapy problems improved, #high-risk medication problems improved, #PIMs improved	I/C					I/C
Adverse drug event assessment						I/C
Patient problems with medications						I/C
Patient/caregiver satisfaction questionnaire						I/C
Provider satisfaction questionnaire						I/C
Health Resource Utilization Questionnaire						I/C

Abbreviations: *A*-all potentially eligible patients, *B-*all eligible and interested patients, *I*-intervention, *C*-control, *I/C*-both groups

